| Abstract | Chronic pelvic pain syndrome (CPPS) has a high incidence and can present with severe symptoms, leading to mental health issues, causing anxiety, depression, and pain catastrophizing, and placing significant stress on families and society. The exact causes and mechanisms of CPPS remain unclear; studies suggest it may be caused by psychological issues and multi-system dysfunction. Therefore, addressing psychological problems is crucial in the treatment of CPPS. Repetitive peripheral magnetic stimulation (rPMS) shows potential effectiveness in treating CPPS, while repetitive transcranial magnetic stimulation (rTMS) has been proven to be effective for anxiety and depression. This study employs a randomized, double-blind method, recruiting 66 CPPS participants with accompanying psychological issues, who are stratified by gender and randomly assigned to three groups (1:1:1): double-target magnetic stimulation group, peripheral magnetic stimulation group, and sham stimulation group, receiving the corresponding treatments. The efficacy and safety of double-target magnetic stimulation in CPPS patients with psychological disorders will be assessed by comparing changes in pelvic pain scores (for females) or the National Institutes of Health Chronic Prostatitis Symptom Index (NIH-CPSI, for males), depression, anxiety, and stress scales (DASS-21), pelvic floor surface electromyography, pudendal nerve motor evoked potentials, and the 36-item Short Form Health Survey (SF-36) scores before and after treatment. | | | | | | | | | | |
| Keywords | | Repetitive Transcranial Magnetic Stimulation, Repetitive Peripheral Magnetic Stimulation, Chronic Pelvic Pain Syndrome, Randomized Controlled Trial | | | | | | | | | |

**三.**Project Team Members (including Principal Investigators)

| Name | Unit | Dgree | Title | Task division | Ethics training | GCP training | Signature |
| --- | --- | --- | --- | --- | --- | --- | --- |
| [name] | Chengdu Anorectal Hospital | Master's degree | Associate Chief Physician | Project Leader | Yes | Yes |  |
| [name] | Chengdu Anorectal Hospital | Doctor | Professor | Project Guidance | Yes | Yes |  |
| [name] | Chengdu University of Traditional Chinese Medicine Affiliated Hospital | Doctor | Chief Physician | Supervision of Project Implementation | Yes | Yes |  |
| [name] | Sichuan Province Fifth People's Hospital | Master's degree | Attending physician | Data organization, statistical analysis | Yes | Yes |  |

| 1. Features and Innovations of this Project  This study employs a prospective randomized controlled trial design, setting up a control group experiment. The control group will consist of CPPS patients receiving sham stimulation and those receiving peripheral magnetic stimulation, while the experimental group will consist of CPPS patients receiving dual-target magnetic stimulation. By comparing the clinical safety and efficacy indicators among the three groups of patients, the study aims to explore the therapeutic effects and safety of dual-target magnetic stimulation in CPPS patients with comorbid psychological disorders. Dual-target magnetic stimulation is derived from the author's team's years of clinical experience and in-depth understanding of various CPPS treatment methods. Currently, no relevant studies have been found in domestic and international literature regarding the use of this type of treatment for CPPS patients with comorbid psychological issues.   1. Feasibility Analysis (Department Conditions, Personnel Allocation, Case Sources, Technical Conditions, etc.)   Chengdu Anorectal Specialty Hospital is a tertiary first-class specialty hospital that integrates medical treatment, teaching, research, and preventive healthcare into a medical center. Its anorectal department is a nationally key clinical specialty, and the constipation department and pelvic floor center have a significant influence in the western region of China. The treatment for this clinical research will be conducted at the hospital's pelvic floor center.  Our team has accumulated certain clinical experience in the application effects and safety of peripheral magnetic stimulation in the treatment of CPPS. We have established standardized procedures for using transcranial magnetic stimulation to treat mental disorders such as anxiety and depression. According to relevant reports, the incidence of CPPS has shown an upward trend both domestically and internationally, and the presence of psychological issues is a major reason for its poor treatment outcomes. Therefore, it is particularly important to find effective treatment methods for CPPS patients with coexisting psychological disorders.  The research team currently has 5 senior technical staff members, 8 individuals with a master's degree or higher, and possesses rich experience in clinical research, patient follow-up, and statistical analysis. This ensures the accuracy of clinical data recording and statistical analysis. The talent structure is reasonable, with clear division of labor, which guarantees the smooth completion of this project. |
| --- |

1. Progress schedule and expected goals

| 1. Progress Plan (including annual task objectives, assessment indicators, and the planned progress for completing research and development content. It should be filled out annually, with each year's research plan and objectives being clear, measurable, and corresponding to the overall research tasks, completion timeline, and assessment indicators of the project.)  2024.01-2025.01 ① Successfully enrolled 40 cases of CPPS patients (conducting randomization and providing corresponding treatments), collected relevant clinical indicators and postoperative complication occurrences, and systematically recorded the data.  2025.02-2025.07 ② cases of CPPS patients were successfully enrolled (randomized grouping was conducted, and corresponding treatments were administered). Relevant clinical indicators and postoperative complications of the patients were collected, and the data was systematically recorded.  2025.08-2025.10 ③ Conduct statistical analysis on the collected data.  2025.11-2025.12 ④ Write a thesis.  2. Expected Goals and Assessment Indicators (Focus on describing the final outcomes and forms of this research, such as papers, results, patents, etc.; the content of the assessment indicators must be complete and clear, capable of evaluating the degree of completion of the project and its actual effects.)  (1) Investigate the application effects and safety of dual-target magnetic stimulation in the treatment of CPPS patients.  (2) Publish 2 SCI articles related to clinical research. |
| --- |

**七．Budget allocation**

| Serial Number | Budget Item Name | Budget (in ten thousand) | Remarks (Basis and Explanation of Calculations) |
| --- | --- | --- | --- |
| 1 | Clinical research business expenses | 3 | The costs for the preparation of the project proposal and CRF form, training fees for research assistants and researchers, labor costs for graduate students, expenses for external study, literature retrieval, and other related costs. |
| 2 | Consultation fees, research fees, and labor fees | 1 | Expert consultation fees, publication of papers, editing, follow-up fees for enrolled case investigations, etc. |
| 3 | Data fee | 0.3 | Copying and printing fees, data statistical analysis fees, etc. |
| 4 | Collaboration fee | 0.5 | The expenses incurred for collaboration or research during the implementation of the project. |
| 5 | Transportation expenses | 0.2 | Transportation expenses for studying abroad. |
|  | Total | 5 |  |

**Peripheral combined central dual-target magnetic stimulation for rehabilitation of chronic pelvic pain syndrome with psychosomatic disorders: Study protocol for a randomized controlled trial**

Appendix 6 [3](#_Toc15674)8

[Appendix 7 4](#_Toc8090)1

Plan Summary

| Research Title | Peripheral combined central dual-target magnetic stimulation for rehabilitation of chronic pelvic pain syndrome with psychosomatic disorders: Study protocol for a randomized controlled trial |
| --- | --- |
| Principal Investigator | Deputy Chief Physician [name] |
| Research Purpose | This study aims to evaluate the effectiveness and safety of repeated peripheral magnetic stimulation (rPMS) combined with repeated transcranial magnetic stimulation (rTMS) in treating patients with pelvic pain syndrome accompanied by psychological disorders. It will assess the impact of dual-target magnetic stimulation on patients' pelvic pain scale/NIH-CPSI scores, depression, anxiety, and stress (DASS-21) scores, as well as the SF-36 quality of life scale, and the effects on pelvic floor muscle surface electromyography and pudendal nerve motor evoked potentials. Additionally, it will compare the effects of dual-target magnetic stimulation and peripheral magnetic stimulation on pain levels, psychological status, and quality of life in patients with chronic pelvic pain syndrome accompanied by psychological disorders, providing a basis for clinical treatment options. |
| Main evaluation indicators (efficacy indicators) | Pelvic Pain Scale (Female) / NIH-CPSI (Male) |
| Secondary evaluation indicators (efficacy indicators) | Surface electromyography of the pelvic floor muscles  Pudendal nerve motor evoked potentials  Depression Anxiety and Stress Scale (DASS-21)  SF-36 Quality of Life Scale |
| Safety indicators | Complete Blood Count (CBC)  Liver and kidney function  Electrocardiogram |
| Selection Criteria | (1) Meets the diagnostic criteria for Chronic Pelvic Pain Syndrome (CPPS) according to the European Association of Urology (EAU) guidelines for chronic pelvic pain (2022 edition).  (2) Age: 18-70 years old.  (3) Generalized Anxiety Disorder or Major Depressive Disorder that meets DSM-5 criteria.  (4) No significant pathological changes were observed in the physical examination and auxiliary examinations.  (5) No other treatments except for oral medications in the three months prior to the visit.  (6) The patient is informed and voluntarily participates in the study. |

| Exclusion Criteria | (1) Patients with acute systemic and intracranial hemorrhagic diseases.  Individuals with severe underlying health conditions, such as cardiovascular, liver, kidney, respiratory, and blood diseases, as well as malignant tumors and other progressive diseases.  (3) Patients with cardiac metal membranes, cardiac pacemakers, intracranial metal implants, lumbar metal implants, and implantable electronic devices.  (4) Individuals with infections in the head or sacral region.  (5) Individuals exhibiting unstable vital signs.  (6) Patients who have had adverse reactions to magnetic therapy.  (7) Individuals with atypical autonomic reflexes.  (8) Patients with cognitive impairments who cannot cooperate.  (9) Pregnant or breastfeeding women.  (10)Patients with a history of diseases that lead to peripheral nerve damage.  (11)Patients with serious illnesses, such as malignant effusion, active tuberculosis, cancer, or myasthenia gravis.  (12)Patients with severe mental illness or epilepsy. |
| --- | --- |
| Exit Standard | Participants will be asked to withdraw from the RCT under the following circumstances:  (1) If the patient does not adhere to the prescribed treatment plan or receives alternative treatment;  (2) If the patient experiences severe adverse reactions or changes in their condition that prevent them from continuing to participate in the trial;  (3) If the patient experiences significant organ dysfunction, unstable blood pressure, abnormal heart rate, or difficulty breathing;  (4) If the patient requests to withdraw informed consent due to intolerable adverse reactions or for no specific reason;  (5) If the patient loses follow-up during treatment or follow-up. |
| Sample size verification of subjects | According to the research by Yang Jing-ming and his colleagues, under the conditions of β=0.1 and α=0.05, the effect size is 0.5. Pain scores will be used as the primary measurement standard, and G*Power 3.1.9.7 will be used to estimate the sample size. After calculations, it is determined that there will be approximately 54 patients in the study cohort. Considering a 10% dropout rate, each group will include 22 people, and this RCT will require 66 participants. |
| Treatment plan | (1) Double-target magnetic stimulation group treatment procedure: ① Before treatment: Three checks and seven pairs, conducted by a qualified practitioner for risk assessment, including the patient's mental symptoms, medication treatment effects, and contraindications, etc. ② During treatment: Determine the stimulation plan: individualized stimulation intensity, measure the resting motor threshold during the first treatment.  Rest motor threshold (RMT) determines the magnetic stimulation intensity for the patient, with the rTMS stimulation intensity set at 120% of RMT. Auxiliary positioning devices: based on the positioning cap, the location of the stimulation cortex is determined; for depressed patients, the left DLPFC is selected for 10Hz high-frequency stimulation, while for anxious patients, the right DLPFC is selected for 1Hz low-frequency stimulation. The chair is adjusted to a horizontal position of 10-20°, and the patient lies prone on the chair, with the center of the circular coil aligned with the S3 region. During stimulation, a contraction sensation in the anal sphincter muscles and a plantar flexion response indicate correct positioning. rPMS is performed first, followed by adjusting the chair to a sitting position for rTMS. After the treatment is completed, the patient is asked about any discomfort, and elderly patients are advised to sit by the bedside for a moment before leaving. The doctor completes all types of record forms and keeps them for future reference; the treatment room is disinfected and isolated.  (2) Peripheral magnetic stimulation group: ① Before treatment: same as the double-target magnetic stimulation group. ② During treatment: only rPMS is performed, with the same operation as the double-target magnetic stimulation group. ③ After treatment: same as the double-target magnetic stimulation group.  (3) Sham stimulation group: ① Before treatment: Same as the dual-target magnetic stimulation group. ② During treatment: Use coils that do not generate a magnetic field, only producing sound, first applying sham peripheral magnetic stimulation to the S3 region, followed by sham transcranial magnetic stimulation, with the same procedure as the dual-target magnetic stimulation group. ③ After treatment: Same as the dual-target magnetic stimulation group.  (4) Treatment regimen: A course consists of 20 sessions, with 5 sessions per week, and 1 session each day; patients need to actively inform the therapist when there are significant adjustments to the types and dosages of medications.  (5) Emergency Situation Handling: The system should provide protective measures in accordance with the requirements of GB9706.1-2007, such as an emergency braking device. During the treatment process, if unexpected seizures, loss of consciousness, or other emergencies occur, immediately take the following measures for handling and first aid: ① Immediately stop rTMS treatment; ② Ensure the patient's airway is clear; ③ Closely monitor the patient's vital signs; ④ For cardiac arrest or respiratory failure, immediately perform cardiopulmonary resuscitation; ⑤ Contact the patient's family to inform them of the situation and the corresponding handling measures. After the emergency situation is resolved, summarize the experiences and lessons learned. |

1. Basis for the Topic

Chronic Pelvic Pain Syndrome (CPPS) refers to persistent or recurrent pain in the pelvic region lasting more than three months, without confirmed infection or other obvious local pathological causes to explain the pain. It is often associated with negative cognitive, behavioral, sexual, and emotional consequences, as well as symptoms suggesting lower urinary tract (LUT), sexual, intestinal, pelvic floor, or gynecological dysfunction^[1]^. In men, the global prevalence of CPPS ranges from 2% to 16%^[2]^; while in women, the global prevalence of CPPS can be as high as 24%^[3]^. A series of pelvic floor functional disorders, such as chronic pelvic pain syndrome, have diverse and difficult-to-discuss symptoms that can severely impact patients' social activities and quality of life, leading to issues such as low self-esteem and depression, thereby increasing pressure on families and society^[4]^. One statistic estimates that the annual cost of treating CPPS is approximately $880 million^[5]^.

The exact cause and pathogenesis of Chronic Pelvic Pain Syndrome (CPPS) remain unclear; it may be the end result of the interaction between psychological disorders and multi-system dysfunction ^[6]^. Some studies suggest that chronic pelvic pain syndrome is a manifestation of pelvic floor dysfunction, and its occurrence and development are related to pelvic floor neuromuscular injury ^[7]^. In 85% of patients, the chronic pain syndrome originates from muscle ^[8]^. Muscle overactivity is a characteristic of chronic pelvic pain syndrome and is a major cause of pain ^[9]^. The symptoms of CPPS can severely affect the psychological state of patients, leading to issues such as anxiety, depression, and pain catastrophizing ^[10]^. Psychosocial factors not only directly lead to the occurrence and development of mental disorders but also influence the outcome of somatic diseases. Psychological factors have always been considered relevant in the maintenance of persistent pelvic and urogenital pain ^[11]^. The United Nations Pain Association describes chronic pain as an "unpleasant sensory and emotional experience," which requires psychosocial treatment. This treatment model recognizes the impact of mind-body regulation on pain ^[12]^.

Patients with Chronic Pelvic Pain Syndrome (CPPS) often exhibit hypersensitivity in both the central and peripheral nervous systems, leading to dysfunction in pain regulation, which can exacerbate pain^[13-18]^. Currently, treatment for pelvic pain is primarily based on its etiology and often involves physical therapy, medication, and nerve blocks. For refractory cases, neuromodulation can be applied to the central and peripheral nervous systems^[19]^. Two systematic reviews have evaluated the effects of neuromodulation techniques on CPPS. Both studies concluded that neuromodulation may be effective in alleviating pain and improving the quality of life for patients with CPPS^[20,21]^. Magnetic stimulation can generate small electrical currents in deep neural structures to non-invasively activate these structures (it can be used to detect nerve stimulation and serves as a non-invasive clinical tool for modulating and treating neural function). Some studies have reported that applying 8000 pulses of magnetic stimulation to painful areas in patients with localized musculoskeletal injuries can reduce pain^[22]^. Other research indicates that magnetic stimulation of the sacral nerve roots can significantly improve pudendal neuralgia and sciatica^[23]^. One study showed that magnetic stimulation with specific parameters applied to the peripheral nerves in the pelvic region can inhibit or activate neural pathways and modulate abnormal reflex arcs, thereby affecting the functions of the urethra, bladder, rectum, anus, and pelvic floor muscles^[24]^. Transcranial magnetic stimulation (TMS) is rapidly gaining popularity due to its specificity in modulating brain function and its status as a painless, safe, and reliable treatment method. Repetitive TMS (rTMS) therapy is used globally for patients with depression, with high-frequency rTMS (HF-rTMS) applied to the left dorsolateral prefrontal cortex (DLPFC) showing clear antidepressant effects^[25]^. The U.S. Food and Drug Administration (FDA) first approved this application on December 16, 2008; on the other hand, the benefits of rTMS have been reported to be advantageous for mood in elderly samples^[26]^. Low-frequency rTMS (LF-rTMS) applied to the right DLPFC significantly reduces generalized anxiety, improves self-reported emotional regulation, and enhances sleep quality^[27-29]^.

Research indicates that repetitive peripheral magnetic stimulation (rPMS) may be effective in treating chronic pelvic pain syndrome (CPPS), while repetitive transcranial magnetic stimulation (rTMS) has therapeutic effects on anxiety and depression. However, the articles on peripheral magnetic stimulation for CPPS are mostly observational studies or small sample studies, and there is currently a lack of high-quality research on the treatment of chronic pelvic pain syndrome with peripheral magnetic stimulation. Additionally, the presence of comorbid psychological disorders has not been taken into account. Therefore, we conducted this study to evaluate the efficacy and safety of rPMS combined with rTMS in CPPS patients with comorbid psychological disorders, and to provide more treatment options for CPPS patients with such comorbidities.

References:

[1] D. Engeler, A.P. Baranowski, B. Berghmans, J. Birch, J. Borovicka, A.M. Cottrell, P. Dinis-Oliveira, S. Elneil, J. Hughes, E.J. Messelink, R.A. Pinto, M.L.v. Poelgeest, V. Tidman, A.C.d.C. Williams, P. Abreu-Mendes, S. Dabestani, B. Parsons, J. Tornic, V. Zumstein, EAU Guidelines on Chronic Pelvic Pain, 2022.

[2] C. Smith, Male chronic pelvic pain: An update, Indian Journal of Urology 32(1) (2016).

[3] P. Latthe, M. Latthe, L. Say, M. Gülmezoglu, K.S. Khan, WHO systematic review of prevalence of chronic pelvic pain: a neglected reproductive health morbidity, BMC Public Health 6(1) (2006).

[4] J. Kwon, H.J. Lee, J.H. Joo, E.C. Park, Urinary incontinence status changes and depressive symptoms among middle-aged and older women: Using data from a survey of the Korean Longitudinal Study of Aging, Journal of affective disorders 279 (2021) 549-553.

[5] W. Stones, Y. Cheong, F.M. Howard, S. Singh, Interventions for treating chronic pelvic pain in women(Review), Cochrane Collab 11 (2010) 1-43.

[6] K. Grinberg, Y. Sela, R. Nissanholtz-Gannot, New Insights about Chronic Pelvic Pain Syndrome (CPPS), International Journal of Environmental Research and Public Health 17(3005) (2020).

[7] P. Enck, D.B. Vodusek, Electromyography of pelvic floor muscles, Journal of electromyography and kinesiology : official journal of the International Society of Electrophysiological Kinesiology 16(6) (2006) 568-77.

[8] A.J. Slomski, How groups successfully manage pain patients, Medical economics 73(1) (1996) 112, 115-6, 119-20 passim.

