3.3 Exit Standards

Participants will be asked to withdraw from the RCT under the following circumstances:

(1) If the patient does not adhere to the prescribed treatment plan or receives alternative treatment;

(2) If the patient experiences severe adverse reactions or changes in their condition that prevent them from continuing to participate in the trial;

(3) If the patient experiences significant organ dysfunction, unstable blood pressure, abnormal heart rate, or difficulty breathing;

(4) If the patient requests to withdraw informed consent due to intolerable adverse reactions or for no specific reason;

(5) If the patient loses follow-up during treatment or follow-up.

4. Plan Design

This study employs a prospective, randomized, blind, controlled trial design.

5. Sample Size Estimation and Grouping

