6.3 Peripheral Magnetic Stimulation Treatment Protocol

Implement rPMS according to the same procedure as the dual-target magnetic stimulation group. All parameters are the same as those in the dual-target magnetic stimulation group.

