14.4 Setting up the experimental blind method

A researcher will place the random sequence numbers generated by SPSS software into opaque envelopes separately and number the envelopes in order on the surface. This researcher will not participate in other studies and will ensure that the envelopes containing the random sequence numbers remain sealed throughout the research process, so that other personnel will not know the random sequence numbers inside the sealed envelopes in advance. A second researcher will select eligible patients for the study based on inclusion and exclusion criteria. Patients will be informed of the potential benefits and risks of the study, and if they agree to participate, they will sign an informed consent form. The third researcher will ask patients about their condition, assess their status, assist in filling out the CRF forms, and distribute the envelopes to the patients participating in the study. The fourth researcher will treat patients according to the random sequence numbers in the envelopes given to them and will not participate in other studies. The fifth researcher will evaluate and complete the pelvic pain scale (for women) / National Institutes of Health Chronic Prostatitis Symptom Index (NIH-CPSI) (for men), the DASS-21 scale, and the SF-36 quality of life scale assessments, and will complete the patients' pelvic floor surface electromyography and pudendal nerve motor evoked potential tests. This researcher will not participate in data analysis or other studies. After data collection is completed, the first unblinding will occur, with two researchers entering and verifying the data separately. Finally, a statistical analyst will conduct the statistical analysis, comparing the three groups without knowing the group assignments. After the analysis is completed, a second unblinding will take place, marking the end of the study.

15. Preservation of Data and Records

Researchers are responsible for ensuring that research records are not accidentally damaged; the medical records of subjects should be clearly labeled to prevent accidental destruction of documents due to errors. Researchers and research institutions must retain clinical trial-related materials for five years after the conclusion of the clinical trial. Original medical documents should be kept according to the relevant regulations of the hospital, but must not be less than five years after the conclusion of the clinical trial.

16. Research Process

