All subjects must meet the diagnostic criteria for CPPS according to EAU and the diagnostic criteria for generalized anxiety disorder or major depressive disorder according to DSM-5. Subjects who are determined to meet the inclusion criteria and do not fall under the exclusion criteria are considered potential subjects. The screening physician will inform the subjects and their families about the study, explain the differences in treatment, and seek the opinions of the subjects and their families on whether they agree to random grouping. Patients who agree to random grouping will sign an informed consent form and will then be included in the study for random grouping and will receive follow-up after the treatment course. (See Appendix 1)

17. Summary report and paper publication

(1) After completing the research summary of the clinical study, papers can be published and participation in domestic and international academic conferences is possible.

(2) The results of this research will be published in the form of papers. It is expected to publish 1-2 SCI papers.

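### The trial is labelled double-blind, but the peripheral arm has no sham rTMS, so dual-target versus peripheral is not patient-blinded and is unequal in procedure time

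*Protocol*

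**What the plan says.** The abstract in the application form states: "This study employs a randomized, double-blind method". Section 4 is less specific: "This study employs a prospective, randomized, blind, controlled trial design".

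The procedures by arm are as follows.

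- **Dual-target** (Plan Summary, Treatment plan item 1; section 6.2): "rPMS is performed first, followed by adjusting the chair to a sitting position for rTMS". The head site follows the diagnosis: left DLPFC for major depressive disorder, right DLPFC for generalized anxiety disorder.
- **Peripheral** (Plan Summary item 2): "only rPMS is performed, with the same operation as the double-target magnetic stimulation group". Section 6.3 agrees: "Implement rPMS according to the same procedure as the dual-target magnetic stimulation group".
- **Sham** (Plan Summary item 3; section 6.4): a coil that makes sound but no field, used first at S3 and then at the head.

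Section 16 has the screening physician "explain the differences in treatment" before the patient signs consent. Section 14.4 separates the person who treats from the person who evaluates and the person who analyses. On the handling of the code it says: "After data collection is completed, the first unblinding will occur, with two researchers entering and verifying the data separately". A blind analysis and a second unblinding follow.

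**The concern.** A patient who knows how the treatments differ, and whose head is never approached in 20 sessions, has good reason to conclude that he or she is in the peripheral arm. The other two arms cannot be told apart by counting procedures, but both can be told from this one. So the double-blind claim conflicts with the peripheral procedure.

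This matters because the Plan Summary and section 2 name dual-target versus peripheral, on pain, psychological state and quality of life, as a comparison meant to guide treatment choice. The primary scales (Appendices 3 and 4), DASS-21 and SF-36 all rest on the patient's own ratings, and a separate evaluator does not shield those from what the patient believes. A difference between these arms could reflect active rTMS, expectation, the added procedure time, or a mixture. No later choice of analysis can separate them.

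**Working it through.** **Procedures side by side**

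| | Dual-target | Peripheral | Sham |
|---|---|---|---|
| S3 step | active | active | sham |
| Head step | active | none | sham |
| Procedures per session | 2 | 1 | 2 |

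What a patient can infer from procedure count alone:

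- One procedure: peripheral arm.
- Two procedures: dual-target or sham, not peripheral.

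Dual versus sham is therefore balanced on procedure count. The two comparisons that involve the peripheral arm are not.

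**Time.** The protocol states no session length, so there is no figure of its own to reproduce. Time can be derived from the parameters in section 6.1(5):

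- pulses per train = frequency × seconds on
- trains = total pulses ÷ pulses per train
- time = trains × (seconds on + interval)

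| Step | Pulses per train | Trains | Time |
|---|---|---|---|
| rPMS, 20 Hz, 2 s on, 28 s interval, 1600 pulses | 20 × 2 = 40 | 1600 ÷ 40 = 40 | 40 × 30 s = 20 min |
| Right DLPFC, 1 Hz, 10 s on, 2 s interval, 1000 pulses | 1 × 10 = 10 | 1000 ÷ 10 = 100 | 100 × 12 s = 20 min |
| Left DLPFC, 10 Hz, 4 s on, 26 s interval, 3000 pulses | 10 × 4 = 40 | 3000 ÷ 40 = 75 | 75 × 30 s = 37.5 min |

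Leaving out the final interval changes little: 19.5, 20.0 and 37.1 min.

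Per session:

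- Peripheral arm: 20 min.
- Dual-target or sham arm, anxiety: 20 + 20 = 40 min.
- Dual-target or sham arm, depression: 20 + 37.5 = 57.5 min.
- Excess over the peripheral arm: 20 min (anxiety) or 37.5 min (depression).

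Over the 20 sessions in section 6.1(7): 20 × 20 = 400 min, or 20 × 37.5 = 750 min. The average excess lies between these and depends on the mix of diagnoses, which the protocol does not fix. If a sham head step of matching length were added to the peripheral arm, the difference would be 0 min.

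**Outcomes exposed.** The Pelvic Pain Scale, NIH-CPSI, DASS-21 and SF-36 are patient-rated. Pelvic floor EMG and pudendal motor evoked potentials are instrumental and less exposed, but they are secondary.

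**The case against.** The best defence is that comparing a two-site package with rPMS alone, each as it would be delivered, is a legitimate question. The objectives speak of informing treatment options and do not promise to isolate rTMS. Section 4 says only that the trial is blind, and section 14.4 keeps evaluator and analyst apart from treatment. Dual-target versus sham, which serves the aim of evaluating the combination, is matched. All of this stands. It supports an honestly labelled package comparison, but not the double-blind label for the peripheral arm.

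Four stronger readings are tempting, and the documents do not carry them.

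- **That every peripheral patient is certainly unblinded.** Section 16 says treatment differences are explained, but the consent text is not available here, so how much patients learn about each procedure cannot be checked. The supportable word is probably.
- **That the extra minutes are staff contact.** They are stimulation cycles, much of them intervals between trains. The protocol gives no contact time.
- **That data entry and the analyst are unblinded.** Section 14.4 places a first unblinding before data entry, but a blind analysis and a second unblinding follow, so a release of group codes only is a coherent reading. Appendix 7 prints the meaning of letters A, B and C, yet nothing says the analyst receives those letters. The wording is ambiguous; a leak is not established.
- **That sham rTMS would make the trial double-blind.** Active rPMS produces felt muscle contractions that a coil without a field does not, and the treating researcher acts on the allocation.

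**Conclusion.** The point holds. The double-blind label contradicts the procedure for one of three arms, 22 of 66 planned patients. Dual-target versus peripheral and peripheral versus sham are open to expectation bias on the patient-rated outcomes, including the primary ones. They also differ by 20 or 37.5 min of stimulation-cycle time per session (400 to 750 min per course). Dual versus sham is matched for procedures and time.

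This rests on three assumptions: that the treatment explanation lets patients recognise a missing head procedure; that each patient is stimulated at one head site, according to one diagnosis; and that the treatment chart in Appendix 1, which cannot be seen here, adds no sham head step to the peripheral arm. The last would in any case contradict the text of the Plan Summary. The direction and size of any bias in the scores cannot be derived from the protocol.

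**What to change.** 1. In Plan Summary item 2 and section 6.3, have active rPMS followed by sham rTMS with the sound-only coil, at the site and for the duration that the patient's diagnosis would give in the dual-target arm. The coil and the procedure are already in use for the sham arm. The cost is an amendment, consent wording, and 20 to 37.5 min more chair time per session for about 22 patients.
2. Replace the bare term double-blind in the abstract with a statement by role: whether patient, treating researcher, evaluator and analyst are each blinded. This is needed even with step 1, for the reasons given above about sensation and the treating researcher.
3. If step 1 is not adopted, drop double-blind and state that dual-target versus peripheral is not patient-blinded and cannot separate the rTMS effect from expectation and added procedure time. This costs only wording.
4. Minor: in section 14.4, say that the first unblinding releases only neutral group codes, different from the A, B and C of Appendix 7, and place it after the database lock in section 11.1.3. This costs almost nothing.
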